### Sample Size Estimation

To estimate the power of specific paths in the model, an empirical simulation approach was used [82,83]. To run power analysis for LGM models, Muthén and Muthén [83] proposed a general framework using Monte Carlo simulation. Further, 2 separate a priori power analyses were conducted to determine whether a sample size of 300 is sufficient to detect the cross-lagged effects of interest. The first model assumed data were normally distributed and the second model assumed nonnormality in 10% (n=30) of the cases. For each simulation, a sample size of 300 was specified with 10,000 replications successfully completed. For both the normally distributed and nonnormally distributed data scenarios, all estimated parameters had between 82% and 86% coverage, and the parameter estimate and SE bias were below 5%, suggesting sufficient power.

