As with any longitudinal study, attrition is expected. Patterns of missing data and potential bias at time 2 and time 3 will be investigated by comparing demographics and variable scores of participants who are missing to those who are not missing at each time point. In addition to noting and acknowledging any bias due to missingness, the SEM modelling procedure uses a maximum likelihood estimator which also provides one of the best ways to estimate the model parameter estimates in the presence of missing data. While there is no guarantee that the data are missing completely at random, in longitudinal designs, data from earlier time points compensates for the missingness at later time points in the estimation procedure.

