## Results

As illustrated in Figure 3, a total of 571 primary caregivers completed eligibility surveys (Guelph n=298; Hamilton n=273). Of those, 129 did not enroll in this study: 119 did not meet inclusion criteria, 8 declined to participate, and 2 were excluded for incomplete registrations. Of the 442 eligible families enrolled (ie, provided consent), 79 did not complete any baseline measures (ie, did not start this study) and 4 withdrew. Baseline health and behavior surveys were completed for 359 families including 359 primary caregivers (96% women [n=346]), 179 secondary caregivers (92% men [n=166]), and 359 children. Diet recalls were completed for 313 children and 226 children had valid activity monitor wear time (minimum of 360 min for a minimum of 3 days). A total of 301 families completed an at-home health assessment which included anthropometric measures for 301 primary caregivers, 168 secondary caregivers, and 301 children along with the collection of 268 hair samples from the children. Of the 359 families who completed baseline health and behavior surveys, 79% (n=284) identified that they heard about this study through social media, including posts by community organizations that served families and through paid Facebook advertisements.

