## Discussion

### Principal Results

Despite public health restrictions due to COVID-19, which prevented in-person recruitment, the Family Stress Study was successful in recruiting 359 families into the Family Stress Study cohort, and 301 of those families completed all baseline measures for their child. Web-based recruitment, in particular partnering with various community organizations that serve families with young children, was critical to the recruitment success during this time when in-person engagement was limited. Identifying creative ways to connect and share information with families was also needed to ensure effective data collection. This included having research staff connect regularly with families via email, text, or phone to provide them with support throughout the data collection process and by providing information about using accelerometers to measure physical activity in a family-friendly video that could be shared remotely. These approaches were well received by families and could help inform future family-based research using remote recruitment and data collection.

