### Limitations

Although successful in engaging the required sample size, the use of remote recruitment strategies may have impacted the socioeconomic diversity of the sample. While a previous family-based intervention study found that web-based recruitment of families with young children resulted in equivalent participant demographics to traditional recruitment strategies (eg, in-person or via practitioners) [84], other intervention [85] and noninterventional [86] family-based obesity studies have found that in-person recruitment was critical to engaging families, particularly low-income families. Thus, it is possible that had in-person recruitment been possible, more low-income families could have been recruited. Nearly half of the families in the sample reported an annual household income greater than CAD $100,000, which may limit the generalizability of the findings to more socioeconomically disadvantaged families. However, the median income of the sample was CAD $102,800, which is similar to the 2020 median household income (before taxes) for families in Guelph and Hamilton, which was CAD $114,000 and CAD $107,000, respectively [87]. Similarly, in our sample 73.1% (n=263) of the children identified as White, which is similar to the 2021 census data for Guelph and Hamilton which was 73.1% and 72.6%, respectively [87], suggesting that the annual household incomes and race or ethnicity of the children in our sample may be representative of the overall population within these cities.

The need to use remote data collection for the primary outcome, child adiposity, is also a limitation of the Family Stress Study. While the protocols are based on validated methods, the use of caregiver assessments may result in greater error in child adiposity measures than if using researcher-led assessments and this could lead to misclassification for some children. However, the use of caregiver-led assessments allowed the researchers to feasibly implement this study during the COVID-19 pandemic, which represented an unprecedented disruption to family life and associated increase in family stress.

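### The statement that 301 families completed all baseline child measures contradicts the article's own counts, and power at N=300 is not shown for the cortisol and accelerometer mediation paths

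*Protocol article*

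**What the plan says.** All references are to the protocol article.

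- **Sample Size Estimation.** The simulations were run to "determine whether a sample size of 300 is sufficient to detect the cross-lagged effects of interest". Two data scenarios are given: "The first model assumed data were normally distributed and the second model assumed nonnormality in 10% (n=30) of the cases". For both, "For each simulation, a sample size of 300 was specified with 10,000 replications successfully completed". The result, 82% to 86%, is labelled coverage and read as sufficient power. Neither scenario is described as containing missing data.
- **Data Analyses.** Attrition is expected, with no rate given. Missing values are handled by maximum likelihood within the structural equation model, on the argument that earlier waves make up for gaps in later ones. The check on missingness is confined to follow-up: "Patterns of missing data and potential bias at time 2 and time 3 will be investigated". Child cortisol and child behaviors are the two mediators, on a path from exposure at T1 through mediator at T2 to outcome at T3.
- **Results.** Baseline surveys cover 359 families and diet recalls 313 children. The at-home assessment yielded anthropometry for "301 children along with the collection of 268 hair samples from the children", and "226 children had valid activity monitor wear time (minimum of 360 min for a minimum of 3 days").
- **Principal Results.** "301 of those families completed all baseline measures for their child".
- **Limitations.** "Although successful in engaging the required sample size".

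**The concern.** Two statements in the Discussion present the baseline data as more complete than Results shows. One gives a completeness count that is larger than the number of hair samples. The other says the required size was reached, with no distinction between families recruited and children measured on each mediator.

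Mediation through cortisol and weight-related behaviors is part of the primary objective. The precision of a mediated path depends on how many children have the mediator and the outcome measured, as well as on how many families answered the survey. If the cortisol or activity path turns out null, a reader relying on the Discussion could take it as adequately powered evidence against that pathway, which nothing in the article establishes.

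The missing-data plan adds to this. Its reassurance is that earlier time points inform later ones, and its bias check covers only times 2 and 3. The missingness that the article actually documents is at baseline, where there is no earlier time point.

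**Working it through.** **1. The plan's own figures.** The participant flow in Results reproduces: 571 − 129 = 442 enrolled, and 442 − 79 − 4 = 359 with baseline surveys. The 82% to 86% cannot be reproduced, because the article gives no significance level, path coefficients, variances or missing-data set-up for the simulation.

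**2. Baseline counts (Results) against 359 and against the simulated 300.**

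| Measure | n | % of 359 | % missing | Against 300 |
|---|---|---|---|---|
| Survey (stress, eating behavior, screen time) | 359 | 100 | 0 | above |
| Diet recall | 313 | 87.2 | 12.8 | above |
| Anthropometry (adiposity outcome) | 301 | 83.8 | 16.2 | above by 1 |
| Hair sample | 268 | 74.7 | 25.3 | (300 − 268)/300 = 10.7% short |
| Valid activity record | 226 | 63.0 | 37.0 | (300 − 226)/300 = 24.7% short |

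The survey row counts surveys completed; item-level gaps are not reported.

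**3. How many children can have everything?** The number with all measures cannot exceed the smallest single count.

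- If a monitor worn but failing the wear-time rule still counts as completed, hair gives the limit: min(313, 301, 268) = 268.
- If valid data are required, the limit is min(313, 301, 268, 226) = 226.

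Either way 301 is impossible. It equals the at-home assessment count. The joint count is not reported, so only these upper limits can be stated.

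**4. Room for follow-up loss.** As a head count, 359 families can lose (359 − 300)/359 = 16.4% before falling below 300. Adiposity data, at 301 at baseline, fall below 300 once two of those children are lost (301 − 2 = 299).

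**5. Illustrative size only.** Assume that 82% and 86% are power at N=300, two-sided 0.05, for a single path analysed on complete cases. The noncentrality at 300 is then 1.960 + 0.915 = 2.875 (82%) and 1.960 + 1.080 = 3.040 (86%). Scaling by √(n/300) and taking power = Φ(scaled noncentrality − 1.960):

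- n = 268: √(268/300) = 0.945, giving 2.717 and 2.873, so power is 77.6% to 82.0%.
- n = 226: √(226/300) = 0.868, giving 2.495 and 2.639, so power is 70.4% to 75.1%.

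These figures give no credit to partly observed children, which makes them pessimistic about the baseline gap. They also include no follow-up loss.

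**The case against.** The strongest reply is that the required size was met and that the power figures above do not describe this analysis. Much of that stands.

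- **A reader might infer that the simulation assumed 300 complete children with no attrition.** The article does not say so. It is silent on the missing-data set-up, and a condensed article may leave such settings to the full protocol.
- **A reader might infer that the required sample size was missed.** The article never defines 300 as complete cases on each mediator. Against 300, the 359 families and the 301 children with the primary outcome suffice at baseline, and the Limitations wording is about engaging families.
- **A reader might take 268 and 226, reduced by an assumed dropout, as the mediation samples.** The mediation path uses the T2 mediator, for which no count is given. A child with no baseline hair sample may supply one at T2. Baseline values enter the growth and autoregressive parts of the model, so they matter, but they do not fix the mediation sample.
- **Maximum likelihood keeps partly observed children.** Complete-case scaling therefore gives no estimate of the study's power. It also depends on reading coverage as power.
- **The 226 concerns only activity, sedentary time and sleep.** Diet (313) and the survey-based behaviors (359) are above 300 at baseline.
- **Recruitment and follow-up are finished,** so a new simulation cannot change the design.

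None of this rescues the sentence about 301 families. Nor does it supply a demonstration of power for cortisol or accelerometry under the missingness already seen. A re-run can still change how null results are worded.

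**Conclusion.** The completeness sentence in Principal Results is wrong, with no assumption needed: at most 268 children completed every baseline measure, and at most 226 have valid data on all of them.

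On power, the supportable conclusion is narrower than a failed sample size. The article shows a result for N=300 with no described allowance for missing data. Hair cortisol and accelerometry are already 10.7% and 24.7% below that number at baseline, with attrition expected. Adequate power for the cortisol and accelerometer-based mediation paths is therefore not shown; it is not shown to be inadequate either. The complete-case figures, about 78% to 82% at 268 and 70% to 75% at 226, indicate a possible scale and rest on all the assumptions in the working.

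Confining the missingness review to times 2 and 3 is a real gap, because baseline already lacks 16% of adiposity, 25% of hair and 37% of valid activity data.

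**What to change.** 1. In Principal Results, replace the completeness claim with the counts given in Results, or with the true joint count, saying whether it means completed or valid.
2. In Sample Size Estimation, state what the simulation assumed about missing data.
3. Re-run the simulation under maximum likelihood with N=359, the observed missingness by measure and wave, and the actual follow-up losses. Report power separately for each pathway.
4. In Limitations, restrict the sample-size statement to the number of families engaged, or replace it with the per-path result.
5. In Data Analyses, extend the comparison of missing and observed participants to baseline, and bring predictors of missingness into the model as auxiliary variables.

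No new data are needed. Follow-up closed in April 2024, so the loss figures should be obtainable. The cost is a little simulation and analysis work, some rewording, and a stated power that may be lower for the cortisol and accelerometer paths.

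### The sample-size paragraph gives 82-86% coverage where a power figure is needed; that figure does not fit its own bias statement and is probably mislabelled power

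*Protocol article*

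**What the plan says.** The Sample Size Estimation section sets out to estimate power for specific paths by Monte Carlo simulation. It describes two a priori power analyses, run "to determine whether a sample size of 300 is sufficient to detect the cross-lagged effects of interest". The scenarios differ only in distribution: "The first model assumed data were normally distributed and the second model assumed nonnormality in 10% (n=30) of the cases". For each, "a sample size of 300 was specified with 10,000 replications successfully completed".

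The results for both scenarios are given in one sentence: "all estimated parameters had between 82% and 86% coverage, and the parameter estimate and SE bias were below 5%, suggesting sufficient power". The section states no percentage of replications reaching significance, no alpha and no nominal interval level. No power value appears elsewhere in the article. The Limitations section nevertheless treats the required sample size as having been reached.

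**The concern.** A Monte Carlo study of this kind yields at least two separate quantities for each parameter. Power is the share of replications in which the path is statistically significant. Coverage is the share in which the interval contains the value used to generate the data. A valid 95% interval covers about 95% of the time whether power is 5% or 99%, so coverage cannot support a conclusion about power.

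Taken at face value, 82-86% is also poor coverage at any conventional nominal level, and it sits beside a claim that parameter and standard-error bias are both under 5%. Those two statements are hard to hold together.

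In the article as published, this sentence is the only support for n=300. A reader who later meets a null mediation result will need to know what power was shown. That matters here because the Results section reports 268 hair samples and 226 valid activity-monitor records at baseline. Both are mediator measures, both are below 300, and the Data Analyses section expects further attrition.

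**Working it through.** **Inputs from the Sample Size Estimation section:** n=300; 10,000 replications per scenario; coverage 82% to 86% for all estimated parameters in both scenarios; parameter and SE bias each below 5%.

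**Assumptions, because the article does not state them:** two-sided alpha 0.05; nominal 95% intervals, with 90% also tried; approximately normal sampling distributions.

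Power at n=300 cannot be reproduced, because no path values, alpha or power figure are given. What can be checked is whether the coverage figure fits the rest of the sentence.

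**1. Is the gap simulation noise?** The Monte Carlo SE of a coverage estimate c is sqrt(c(1-c)/10,000).
- At c=0.95 it is 0.0022, so a sound 95% interval should show about 94.6% to 95.4%.
- At c=0.82 it is sqrt(0.82 x 0.18/10,000) = 0.0038.
- The shortfalls from 95% are (0.95-0.86)/0.00218 = 41 and (0.95-0.82)/0.00218 = 60 Monte Carlo SEs. From a 90% level they are 13 and 27.

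It is not noise.

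**2. What coverage does the bias statement imply?** Let k be the ratio of reported to true SE, b the relative parameter bias, and z the true path divided by its SE. Then, for 95% intervals,

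coverage = Phi(1.96k - bz) - Phi(-1.96k - bz).

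| k | b | z | Coverage, 95% interval |
|---|---|---|---|
| 0.95 | 0 | any | 93.7% |
| 0.95 | 0.05 | 3.04 | 93.4% |
| 1.05 | 0 | any | 96.0% |

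With 1.645 in place of 1.96 (90% intervals), k=0.95, b=0.05 and z=3.04 give 87.8%, still above 86%.

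**3. What SE error would produce 82-86%?** With no parameter bias, k = z((1+c)/2) / z(nominal).
- 95% intervals: 1.476/1.960 = 0.753 for 86%, and 1.341/1.960 = 0.684 for 82%. SEs would be about 25% and 32% too small.
- 90% intervals: 1.476/1.645 = 0.897 and 1.341/1.645 = 0.815. SEs would be about 10% and 18% too small.

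All four exceed the 5% that the article states.

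**4. Could parameter bias alone close the gap?** At k=0.95 and b=0.05, 95% intervals fall to 86% and 82% only at z of about 15.2 and 18.7. For 90% intervals, coverage is 86.5% at z=6 and 83.6% at z=10. Power at such z-values is essentially 100%, and it is implausible that every estimated parameter lies there.

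**5. Does coverage track power at all?** A simplified simulation was run: one regression path, n=300, 10,000 replications, normal errors or errors with three times the SD in 10% of cases, and standardized paths from 0 to 0.30. Coverage stayed between 94.4% and 95.0% throughout, while power ran from 5% to over 99%.

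**6. The alternative reading.** If 82% and 86% are power at two-sided 0.05, then z = 1.960 + 0.915 = 2.875 and 1.960 + 1.080 = 3.040. Dividing by sqrt(300) gives standardized paths of about 0.166 and 0.176. This is a one-path approximation for illustration, but nothing in it is strained.

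**The case against.** The strongest reply is that this is a wrong word and not a failed simulation. The section announces power estimation, calls the runs power analyses and closes on power. A range of 82-86% lies just above the conventional 80% target. The incompatibility shown above points the same way. On that reading power at n=300 was computed, and only its label is wrong. This stands as the likeliest explanation. It still leaves the published sentence wrong, and the article offers no means of confirming it.

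The bound of 93-96% is not a theorem. It assumes a 95% level that the article does not state, modest z-values and roughly normal estimates. Skewed estimates or unstable SEs, as can arise with variance components or products of paths, may lower coverage while average SE bias stays small. The supporting simulation is one regression path, not the planned latent growth and cross-lagged model. This also stands, so the right description is practically incompatible, not impossible. Nonnormal data do not explain the figure, because the same range is reported for the normal scenario.

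A condensed article may leave path values and per-parameter output to the full protocol. That is accepted, and their absence is no part of this point. The fault lies in a metric that the article does state and in the conclusion drawn from it.

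A reader might also infer that every path test runs at 14-18% type I error. The documents do not support that. The figure arises only if 82-86% really is coverage of 95% intervals, and only if the coverage seen at the simulated path values also holds at a path of zero.

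**Conclusion.** The sentence is wrong as written on either reading. If 82-86% is power, the label is wrong. If it is coverage, the power conclusion does not follow and the bias statement is very hard to believe. The size of the conflict is about 93-96% expected against 82-86% reported, or SE error of 25-32% against a stated limit of 5% (10-18% at a 90% level). This rests on an assumed 95% or 90% nominal level, modest z-values and approximate normality.

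A reader might go further and infer that the study is underpowered, or that its intervals fail. Neither follows. The article does not show what the power is, which differs from showing that it is low, and mislabelled power remains the more probable account.

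Enrollment closed in December 2021 and follow-up ended in April 2024, so the point concerns the stated justification and how results are read, not the sample size.

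**What to change.** Recheck the existing simulation output and correct the paragraph by naming the metric.

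- **If 82-86% is the share of replications significant at the alpha used:** relabel it as power for the cross-lagged paths, state that alpha, and report coverage separately with its nominal level.
- **If it really is coverage:** withdraw both the conclusion of sufficient power and the bias statement until a power figure supports them. Use an interval method whose simulated coverage is near nominal, before results are reported. Only in this case could type I error be inflated, to roughly 14-18% if the same coverage held for null paths.

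In the first case the cost is reading stored output and rewording one paragraph. In the second it is a rerun of the simulation and a choice of interval method while the analysis is still under way. Neither case calls for a change to the sample size.

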## Results

As illustrated in Figure 3, a total of 571 primary caregivers completed eligibility surveys (Guelph n=298; Hamilton n=273). Of those, 129 did not enroll in this study: 119 did not meet inclusion criteria, 8 declined to participate, and 2 were excluded for incomplete registrations. Of the 442 eligible families enrolled (ie, provided consent), 79 did not complete any baseline measures (ie, did not start this study) and 4 withdrew. Baseline health and behavior surveys were completed for 359 families including 359 primary caregivers (96% women [n=346]), 179 secondary caregivers (92% men [n=166]), and 359 children. Diet recalls were completed for 313 children and 226 children had valid activity monitor wear time (minimum of 360 min for a minimum of 3 days). A total of 301 families completed an at-home health assessment which included anthropometric measures for 301 primary caregivers, 168 secondary caregivers, and 301 children along with the collection of 268 hair samples from the children. Of the 359 families who completed baseline health and behavior surveys, 79% (n=284) identified that they heard about this study through social media, including posts by community organizations that served families and through paid Facebook advertisements.

